### Data collection and management

Data collection and management will be conducted in strict adherence to Good Clinical Practice (GCP) guidelines and applicable data protection regulations. Prior to study initiation, all researchers will undergo standardized training regarding the protocol, outcome assessment tools (specifically the 3D-CAM), and data entry procedures to ensure consistency. Data will be collected at preoperative, intraoperative, and postoperative time points and initially recorded on paper Case Report Forms (CRFs) derived from source documents. These CRFs will capture all required demographic, clinical (including specific perioperative variables such as BIS values, core temperature, intraoperative hemodynamics, estimated blood loss, and duration of pneumoperitoneum), and laboratory parameters, as well as adverse events. Subsequently, data will be transcribed into a secure, password-protected electronic database by designated investigators. To ensure data integrity and accuracy, a double-data entry strategy or independent verification process will be employed to identify and resolve any transcription errors. All participant information will be de-identified and assigned a unique study code; the key linking codes to personal identifiers will be stored separately in a locked cabinet accessible only to the principal investigator. Electronic files will be stored on a secure server with restricted access, ensuring that participant confidentiality is maintained throughout the study, analysis, and dissemination process.

### Plans for collection, laboratory evaluation and storage of biological specimens in this trial/future use

Venous blood samples (5 mL) will be collected by trained medical personnel at the designated baseline and postoperative time points. Immediately following collection, samples will be processed according to a standardized protocol, involving centrifugation to separate plasma, followed by aliquoting into coded, de-identified cryovials to prevent degradation from repeated freeze–thaw cycles. These specimens will be securely stored in a monitored ultra-low temperature freezer at −80 °C until the completion of participant enrollment. To minimize inter-assay variability, the quantification of plasma P-tau 217 and S100β levels will be performed using enzyme-linked immunosorbent assay (ELISA) techniques in batch analyses after all samples have been collected. Regarding future use, subject to the specific optional consent obtained from participants, any residual biological material will be preserved in a biobank for potential future ancillary studies investigating biomarkers of perioperative neurocognitive disorders.

### Statistical analysis

All analyses will be conducted according to the ITT principle, in which all randomized participants will be analyzed in the group to which they were originally assigned, regardless of protocol adherence or the treatment ultimately received. Baseline demographic and clinical characteristics will be summarized to assess the balance achieved between the two groups by randomization. Continuous variables will be presented as means with standard deviations (SDs) or medians with interquartile ranges (IQRs) based on the normality of distribution, while categorical variables will be presented as frequencies and percentages. Between-group comparisons for baseline data will be performed using the independent samples *t*-test, the Mann–Whitney U test, or the *χ*^2^ test (or Fisher’s exact test, as appropriate).

The primary outcome is a binary endpoint, defined as the incidence of POD within the first three postoperative days. The primary hypothesis will be tested using a generalized linear mixed model (GLMM) with a binary logistic link function to estimate the adjusted odds ratio (aOR) and 95% confidence interval (CI) for the EA group compared with the SEA group. The model will be adjusted for three pre-specified baseline covariates: age, ASA physical status, and baseline MMSE score. To account for the clustering effect inherent in the multicenter design, the study center will be included in the model as a random effect. To quantify the clinical effect size, a supplementary analysis will be conducted. We will use a modified Poisson regression model with a robust error variance to directly estimate the adjusted relative risk (aRR) after adjusting for the same covariates. The absolute risk reduction (ARR) and the number needed to treat (NNT), with their corresponding 95% CIs, will then be calculated from the aRR. Missing data on the primary outcome will be handled using multiple imputation by chained equations (MICE) under the missing-at-random assumption.

A comprehensive assessment of efficacy will be conducted by analyzing a series of secondary outcomes. For longitudinal continuous outcomes—such as the HADS-A scores measured at multiple time points—a linear mixed-effects model (LMM) will be used to account for within-subject correlation. For pre-to-post changes in biomarkers (P-tau 217 and S100β), an analysis of covariance (ANCOVA) model will be used, with the baseline value included as a continuous covariate to improve statistical precision. For all other secondary outcomes, continuous variables will be compared using the independent samples t-test or the Mann–Whitney U test; ordinal outcomes (such as CRBD severity) will be analyzed with the Mann–Whitney U test, and binary outcomes will be compared using the *χ*^2^ test or Fisher’s exact test. Safety outcomes, including the incidence of adverse events (e.g., acupuncture-related hematoma, dizziness) and general postoperative complications, will also be compared between the groups using the *χ*^2^ test or Fisher’s exact test. Additionally, to assess the success of blinding, the agreement between participants guessed and actual treatment allocation will be quantified using Cohen’s Kappa coefficient.

Two exploratory analyses will be conducted. First, to identify potential predictors of POD, we will perform separate univariable logistic regression analyses for key intraoperative variables (e.g., duration of anesthesia, estimated blood loss), reporting unadjusted odds ratios and 95% CIs. Second, we will investigate the association between these variables and the treatment effect to generate hypotheses for future research.

We will perform a series of subgroup analyses of the primary outcome to explore the potential heterogeneity of the treatment effect (i.e., effect modification) across patient characteristics. These analyses will be based on age, ASA physical status, and baseline MMSE score. These analyses will be performed by including an interaction term between the treatment assignment and the subgrouping variable in the primary GLMM model. We will primarily focus on the *p* value for the interaction to assess for statistically significant effect modification and present the aORs and 95% CIs for each subgroup in a forest plot. To test the robustness of the primary findings under different analytical assumptions, we will conduct a series of sensitivity analyses. First, to assess the influence of protocol deviations, we will repeat the primary analysis on the Per-Protocol (PP) population. Second, to evaluate the overall impact of covariate adjustment, we will fit a univariable model containing only the treatment assignment and compare its effect estimate (crude odds ratio) with that of our primary multivariable model (aOR). Third, to assess the influence of the statistical modeling of the center effect, we will repeat the analysis treating the study center as a fixed effect rather than a random effect. Finally, to address potential bias from data missing not at random, a “worst-case” scenario analysis will be performed, assuming all missing outcomes in the EA group are events and all in the SEA group are non-events.

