## Methods and analysis

### Trial setting

This study is a two-center, randomized, sham-controlled trial with two parallel arms. The study protocol has been designed in accordance with the Standard Protocol Items: Recommendations for Interventional Trials (SPIRIT) 2013 statement (26). Eligible patients will be enrolled and randomly assigned in a 1:1 ratio to receive either EA or SEA. The trial is currently being conducted at the Affiliated Hospital of Jiaxing University and the Jiaxing Hospital of Traditional Chinese Medicine. Ethical approval was granted by the Ethics Committee of The Affiliated Hospital of Jiaxing University on July 30, 2024 (Approval No. 2024-KY-603) and by the Ethics Committee of the Jiaxing Hospital of Traditional Chinese Medicine on October 28, 2024 (Approval No. S1-2024-0096). The protocol is registered with the Chinese Clinical Trial Registry (Registration number: ChiCTR2500097337). A flowchart illustrating the study procedures is provided in Figure 1. Both groups will receive a standardized perioperative pain relief protocol to minimize confounding factors. Participant enrollment commenced in March 2025 and is anticipated to continue until July 2026. Written informed consent will be obtained from each participant prior to enrollment. The schedule of enrollment, interventions, and assessments is detailed in Table 1.

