### Randomization and blinding

Randomization will be performed by an independent statistician using SPSS software version 26.0, generating a random number sequence to assign participants in a 1:1 ratio to either the EA or SEA group. To ensure a balanced distribution between the two study sites, randomization will be stratified by center utilizing a block randomization method with varying block sizes of 4 or 6. The allocation sequence will be concealed in sequentially numbered, opaque, sealed envelopes, which will be kept in a secure location and opened by the acupuncturist only after the participant has provided informed consent and completed baseline assessments. Given the nature of the intervention, the acupuncturist cannot be blinded to group allocation; however, to minimize bias, this study employs a patient- and assessor-blinded design. Participants will remain blinded to their treatment assignment through the use of a sham procedure with identical device settings (lights and sound), while outcome assessors—including anesthesiologists responsible for intraoperative management and research registrars conducting postoperative delirium assessments—will be strictly blinded to group allocation. Additionally, the statistician performing the final analysis will handle data with coded identifiers to maintain blinding until the analysis is complete, with emergency unblinding permissible only if essential for clinical management of a severe adverse event.

To evaluate the integrity of the blinding procedures, a standardized blinding assessment questionnaire will be administered to all participants immediately following the completion of the intervention. Participants will be required to quantify the intensity of the stimulation sensation—encompassing specific De qi characteristics such as soreness, numbness, distension, or heaviness—and report their perception regarding the nature of the treatment received. The specific details this assessment are presented in Table 2.

**Table 2 tab2:** Questionnaire for the assessment of blinding effectiveness and acupuncture sensation.

Blind Method Assessment Questionnaire
Name:________ Random Number:_________ Date:___________ **Please answer the following questions according to the latest acupuncture experience.**

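### Centre is a random effect with only two centres, so its variance cannot be estimated reliably; making the already planned fixed-centre model primary is a minor, free improvement

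*Protocol article*

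**What the plan says.** All references are to the protocol article.

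- **Trial setting:** "This study is a two-center, randomized, sham-controlled trial with two parallel arms".
- **Randomization and blinding:** "randomization will be stratified by center utilizing a block randomization method with varying block sizes of 4 or 6". Centre is the only stratification factor named.
- **Statistical analysis, primary outcome:** "The primary hypothesis will be tested using a generalized linear mixed model (GLMM) with a binary logistic link function". The model has three baseline covariates (age, ASA status, MMSE score). Centre is specified separately: "the study center will be included in the model as a random effect".
- **Statistical analysis, relative risk:** a supplementary modified Poisson model estimates the relative risk "after adjusting for the same covariates". The absolute risk reduction and number needed to treat are then derived from it. No centre term is named.
- **Statistical analysis, secondary outcomes:** the linear mixed model is described for within-subject correlation and the ANCOVA for the baseline value. The remaining comparisons are simple two-group tests. None mentions centre.
- **Statistical analysis, sensitivity analyses:** the third one repeats the primary analysis "treating the study center as a fixed effect rather than a random effect".

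**The concern.** A random effect treats the centres as a sample from a population of centres and estimates the spread of that population. Two centres give one contrast, hence one degree of freedom, and no reliable estimate of spread. In such data the maximum-likelihood variance is often exactly zero. The fitted model is then an ordinary logistic regression without centre, and the one factor used to stratify allocation has left the confirmatory analysis without anyone having decided that it should.

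The model that always keeps centre is in the plan, but only as a sensitivity analysis, and the plan applies it to the primary outcome alone. What is at stake is whether the primary analysis reliably reflects the randomisation strata.

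**Working it through.** No printed figure in the plan depends on this choice, so there is none to reproduce. The check asks how often the centre variance collapses, and whether that matters for the treatment comparison.

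**Inputs from the protocol article.** Two centres; 1:1 allocation; 212 patients, so 106 per arm; expected incidence 20% (sham) and 8% (electroacupuncture); 101 per arm before allowance for loss.

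**Assumptions.** The article gives neither the centre sizes nor the spread between centres. I take equal centres (53 per arm per centre) and a between-centre SD τ of 0 to 0.8 log-odds. Baseline covariates are left out.

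**Step 1: expected events.** 101 × (0.20 + 0.08) = 28.3; 106 × 0.28 = 29.7. So there are about 28 to 30 events.

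**Step 2: best-case precision of the variance.** Suppose the two centre effects were observed without error. The 95% interval for the variance on 1 degree of freedom runs from 1/5.024 to 1/0.000982 times the estimate, that is, from 0.20 to about 1018 times.

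**Step 3: chance of a zero estimate, by hand.** The information on a centre's log-odds is 53 × 0.20 × 0.80 + 53 × 0.08 × 0.92 = 8.48 + 3.90 = 12.38, so its sampling variance is v = 1/12.38 = 0.0808. With observed difference d between the two centres, the normal-approximation ML estimate of τ² is max(0, d²/4 − v). Since d has variance 2(τ² + v), the estimate is zero with probability P(χ²₁ < 2v/(τ² + v)).

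| Assumed τ | 2v/(τ² + v) | Probability of zero | Simulated share at zero |
|---|---|---|---|
| 0 | 2.00 | 84% | 81% |
| 0.2 | 1.34 | 75% | 73–75% |
| 0.3 | 0.95 | 67% | 62–73% |
| 0.5 | 0.49 | 52% | 52–54% |
| 0.6 | 0.37 | 46% | 37–43% |
| 0.8 | 0.22 | 36% | 29–36% |

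The last column comes from random-intercept logistic fits by maximum likelihood. It gives the range over separate simulation runs, some of them under a null of 20% in both arms. The runs at τ of 0, 0.3 and 0.6 had 150 trials per scenario, so those shares carry Monte Carlo error of up to about 8 percentage points. The formula and the simulations agree adequately.

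**Step 4: effect on the treatment comparison.** Simulations compared random and fixed centre at 20% versus 8% and under a null.

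- Different significance verdict: at most 0.8% of trials.
- Type I error: the same for both models, 3.5% to 5.0% in the runs at τ of 0.2 to 0.8.
- Power: equal to within 0.5 percentage points.
- Treatment standard error, random over fixed: about 0.998.
- Treatment log odds ratio: differences of at most 0.03.

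**Step 5: leaving centre out altogether.** In the logistic model the log odds ratio moved by at most 0.07 at τ of 0 to 0.3 and by at most 0.19 at τ = 0.6; the medians were 0.013 or less. Null rejection was 3.3% to 5.0% in the runs at τ of 0.2 to 0.8, and power fell by at most 2 percentage points, at τ = 0.8. These are logistic results. The modified Poisson model was not simulated.

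**The case against.** The strongest reply is that nothing of consequence changes. A fit that collapses to zero returns an ordinary logistic regression, which is still valid under balanced allocation within centre, and Step 4 shows that the two models nearly always agree. The authors also foresaw the question and will report the fixed-centre model. This stands, and it sets the size of the point.

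Three stronger readings are tempting, and the documents do not support them:

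- A reader might infer that the primary p-value hangs on software behaviour, or that the standard errors fail to match the design. The near-identical standard errors and verdicts in Step 4 do not bear that out.
- A reader might say that the variance cannot be estimated at all. Software will return a value, and in the simulations at τ of 0.2 to 0.8 it was above zero in a quarter or more of trials. It is unreliable, not undefined.
- A reader might call the unstratified t, Mann-Whitney, chi-square and Fisher tests an error. After centre-stratified 1:1 allocation they are common and, if anything, slightly conservative. Stratifying them is a refinement.

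On the modified Poisson model, the reply is that it is only supplementary and that an article may leave a centre term to the analysis plan. That is fair as to weight. As printed, though, the covariates referred to are most naturally the three listed, and centre is not among them.

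The planned sensitivity analysis does not fully answer the point. It leaves the less stable model as primary, and it does not extend to the relative risk and the measures derived from it.

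**Conclusion.** The point holds as a minor one. With two centres, the random-effect variance rests on one degree of freedom, and at the planned size it is estimated as zero in roughly 30% to 75% of trials for an assumed centre SD of 0.2 to 0.8. The stratification factor then drops out of the primary model. The modified Poisson model, as described, leaves it out throughout.

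The consequences for the treatment estimate, its standard error, type I error and power are very small. This is a better-specified analysis available at no real cost; no bias is being corrected.

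The collapse rates depend on the assumed centre SD, equal centres and omitted covariates. The one-degree-of-freedom limit depends on none of these.

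**What to change.** - Make the planned logistic regression with treatment, age, ASA status, MMSE score and centre as a fixed effect the primary analysis. Move the random-effect model to the sensitivity analyses or drop it.
- Add centre as a fixed effect to the modified Poisson model, so that the relative risk and the measures derived from it use the same adjustment.
- Add centre to the secondary linear mixed model and ANCOVA.
- Centre-stratified versions of the simple tests (van Elteren, Cochran-Mantel-Haenszel) are optional.

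The cost is one parameter per model, set against about 28 to 30 expected events for the primary outcome. Only analysis wording changes: no new data, patients or procedures. The change should be recorded before unblinding, so that the choice between the two models does not follow sight of a singular fit.

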
### Sample size

This study aims to investigate whether EA at specific acupoints can reduce the incidence of POD among elderly patients undergoing LRP. The sample size was calculated based on previous reports and our preliminary pilot study. According to earlier research, the incidence of POD in patients undergoing LRP is approximately 21%. In our preliminary pilot study involving 40 elderly patients undergoing LRP (*n* = 20 per group), the incidence of POD was 25% in the sham SEA group and 10% in the EA group. Furthermore, recent evidence in high-risk elderly populations has shown that electroacupuncture can significantly reduce the incidence of postoperative neurocognitive disorders, with reductions comparable to those observed in our pilot data (34). Considering these findings, it is hypothesized that the incidence of POD after treatment will decrease from a baseline of 20% to 8%. With a significance level set at 0.05 and a statistical power of 0.8, the required sample size to detect a significant difference between the two groups is 101 patients per group. Allowing for a potential 5% loss to follow-up, a total of 212 patients will be enrolled in this study.

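### ARR and NNT with their 95% CIs are to be calculated from the adjusted relative risk, which alone determines neither; the most literal conversion makes the ARR interval too narrow at the planned effect

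*Protocol article*

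**What the plan says.** The Protocol article, Statistical analysis, makes a mixed logistic model the primary test and then adds effect measures: "To quantify the clinical effect size, a supplementary analysis will be conducted". The tool is a "modified Poisson regression model with a robust error variance to directly estimate the adjusted relative risk (aRR"), adjusted for the same covariates as the primary model (age, ASA status and baseline MMSE). The next step is stated in one sentence: "The absolute risk reduction (ARR) and the number needed to treat (NNT), with their corresponding 95% CIs, will then be calculated from the aRR".

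The section names no control risk, no standardisation, and no way of carrying the uncertainty of a control risk into the interval. It also does not say that a control risk will be treated as fixed. Missing primary outcomes are to be multiply imputed.

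The design assumptions are under Sample size: "the incidence of POD after treatment will decrease from a baseline of 20% to 8" per cent, and "the required sample size to detect a significant difference between the two groups is 101 patients per group".

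**The concern.** The sentence fixes a route from one number, the aRR, to two absolute measures and their intervals. That route has a missing input. Since ARR = p0 × (1 − RR), where p0 is the risk under sham, the aRR gives an ARR only once a p0 has been chosen and, for the interval, only once the uncertainty of p0 has been dealt with.

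Two things are at stake. First, the article's own control-risk figures differ widely, so one aRR is compatible with very different NNTs, and p0 could be picked after the data are seen. Second, the obvious way to follow the sentence is to multiply one minus each aRR limit by the observed sham risk. This treats a proportion estimated from about 100 patients as a constant. ARR and NNT are the absolute measures that clinicians will read from this trial, so their intervals should have the coverage they claim.

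**Working it through.** **The plan's own figures.** The article states no ARR, NNT or interval. Its planned rates imply RR = 0.08/0.20 = 0.40, ARR = 0.20 − 0.08 = 12 points and NNT = 1/0.12 = 8.3. I take 101 per arm as stated.

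**Step 1: one RR, several ARRs.** ARR = p0 × (1 − 0.40), with control risks that the article itself mentions:

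| Control risk p0 | Source | ARR (points) | NNT |
|---|---|---|---|
| 15.4% | Introduction, low end of range | 9.2 | 10.8 |
| 20% | Sample size, planning value | 12.0 | 8.3 |
| 25% | Sample size, pilot sham group | 15.0 | 6.7 |
| 39.3% | Introduction, high end of range | 23.6 | 4.2 |

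**Step 2: the interval on the literal reading.** The nearest whole counts to the planned rates are 20/101 (p0 = 0.198) and 8/101 (p1 = 0.079).

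- SE(log RR) = √(1/8 − 1/101 + 1/20 − 1/101) = 0.394
- RR = 0.40, 95% CI = 0.40 × exp(±1.96 × 0.394) = 0.185 to 0.866
- Converted ARR limits with p0 held fixed: 0.198 × (1 − 0.866) = 0.027 and 0.198 × (1 − 0.185) = 0.161
- Width 0.135; NNT limits 6.2 to 38

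**Step 3: the interval that carries both arms.**

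- SE(ARR) = √(0.198 × 0.802/101 + 0.079 × 0.921/101) = 0.0479
- ARR = 0.119 ± 1.96 × 0.0479 = 0.025 to 0.213 (Wald)
- Width 0.188; NNT limits 4.7 to 40

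The converted interval is 1 − 0.135/0.188 = 28% narrower. At exactly 20% and 8%, it is 2.8 to 16.3 points, against 2.6 to 21.4 (Wald) and 2.4 to 21.7 (Newcombe).

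**Step 4: why.** To first order the converted interval has variance (p1 × SE(log RR))² = Var(p1) + RR² × Var(p0), whereas the variance of the risk difference is Var(p1) + Var(p0). At RR = 0.40 only 0.40² = 16% of the control arm's variance is counted. At RR = 1 all of it is counted. The shortfall is therefore a function of the effect.

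**Step 5: coverage.** I used 400,000 simulated unadjusted trials per row and left out trials with no events in an arm.

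| True risks (SEA vs EA) | n per arm | Converted interval | Wald interval |
|---|---|---|---|
| 20% vs 8% | 101 | 79.2% | 94.9% |
| 25% vs 10% | 106 | 79.9% | 94.8% |
| 20% vs 12% | 106 | 87.3% | 94.8% |
| 20% vs 15% | 106 | 91.2% | 94.9% |
| 20% vs 20% | 106 | 95.5% | 94.7% |

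In the first row the upper limit falls below the true ARR in 15.4% of trials and the lower limit lies above it in 5.4%, where 2.5% each would be nominal. If p0 is instead a known external value, coverage in that row is about 96%, but for the ARR at that risk.

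**The case against.** The strongest reply is that the faulty method is not written down. The article does not say that the control risk will be held fixed. The modified Poisson model also yields predicted risks for each arm, so the sentence may be shorthand for standardised risks from that model. The choice between delta method and bootstrap, the pooling and the display of the NNT interval are normal content for an analysis plan that is not shown here, so their absence is no fault. The analysis is also supplementary.

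Part of this stands. A reader might infer that the plan commits to a fixed control risk and that its ARR and NNT intervals will be far too narrow whatever the result. The document supports neither. The 79% belongs to one reading at the planned effect, which the article's Discussion itself calls optimistic; at smaller effects the shortfall is modest, and with no effect the converted interval is slightly wider than Wald. A reader might also infer that the method would flatter EA. At the planned effect it would not: the lower limit hardly moves (2.7 against 2.5 points) and the loss is almost all at the largest plausible benefit.

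What does not stand is that nothing needs changing. The sentence names the source of the two measures and of their intervals, and that source is insufficient. If standardisation is meant, the measures come from two risks and their joint variance, and the sentence still needs correcting.

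**Conclusion.** The point holds in limited form. The stated rule cannot be carried out as written, because a relative risk determines neither ARR nor NNT and no control risk is named. If the gap is filled in the most literal way, the ARR interval at 20% against 8% with 101 per arm is about 28% too narrow and covers about 79% instead of 95%. The upper limit is 16.1 instead of 21.3 points.

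These sizes assume that the observed sham risk is plugged in as a constant. They ignore covariates, centre and imputation. They shrink as the true effect shrinks and vanish when there is none. The primary test, the aRR and the interval of the aRR are untouched, so this should be corrected but does not threaten the trial's main conclusion.

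**What to change.** Replace the sentence so that it says the following:

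- From the planned adjusted model, predict each randomised patient's risk under EA and under SEA, and average each set over all randomised patients. ARR is the SEA average minus the EA average. The modified Poisson model already planned suffices; an adjusted logistic model is an alternative.
- Give a delta-method or bootstrap 95% CI that carries the uncertainty of both arms, combined over the multiple imputations.
- Report NNT as 1/ARR with the ARR limits inverted. When the ARR interval includes 0, show the NNT interval as passing through infinity. This could well arise: with 20% against 12% observed in 106 per arm, the Wald ARR interval is −1.8 to 17.8 points, so the NNT interval runs from 5.6 to benefit, through infinity, to 55 to harm.

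With the modified Poisson model and no interaction term, the standardised EA risk equals the aRR times the standardised SEA risk within each completed data set, so the ARR stays consistent with the reported aRR.

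The cost is one sentence and a few lines of code, with no new data and no change to the primary analysis. It should be settled before unblinding.
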